### Outcomes

#### Acceptability

The acceptability questionnaire is adapted from the treatment acceptability and preferences (TAP) validated measure [33]. The TAP is comprised of 4 items: suitability, appropriateness, effectiveness, and willingness to comply, each of which is rated on a 5-point scale ranging from 0 (not at all) to 4 (very much) with higher scores indicating greater acceptability [33]. The total scale score is then obtained by calculating the mean of all the items’ scores. The TAP was shown to have a Cronbach α coefficient greater than .75, supporting good internal consistency [34], and it has been used to evaluate a variety of interventions in different acute and postsurgical care settings [35-37]. The TAP can capture “the complex nature of [participants’] preferences” and yet being simple enough for use in the ICU setting [33]. As recommended [38], 1 item has been added to the questionnaire to determine the risks of side effects of the POMI, an additional important aspect in assessing the acceptability of the intervention.

#### Feasibility of Intervention

The items for the assessment of intervention feasibility include (1) time spent (in minutes) creating the individualized playlist; (2) the presence or absence of any issue with headphone or pillow use; (3) the presence or absence of any issue with music delivery; (4) the presence or absence of skipping one or more songs from the generated playlist; (5) the presence or absence of any environmental noise (eg, alarms and voices) during intervention delivery; (6) the presence or absence of any POMI interruptions; (7) whether the patient participant received the full duration of the POMI; (8) the dose (duration in minutes) of the music delivered; (9) the characteristics of the music delivered (eg, music genres).

Additionally, as part of the feasibility of the intervention, the fidelity of the intervention will be assessed based on specific criteria [39] and will include meeting with participants to discuss music preferences, producing a personalized playlist, and playing music once at least for 20 minutes. Any issues with the delivery of the POMI will also be recorded.

#### Feasibility of Research Methods

The items for the assessment of the feasibility of research methods, based on the CONSORT guidelines for pilot and feasibility RCTs [40,41], include the number of patients screened, number of eligible patients, number of participants recruited, number of participants randomized, and number of participants included in the analysis.

#### Preliminary Efficacy of POMI on Acute Pain

Pain will be assessed at 4 different timepoints for each intervention period: before the intervention, immediately after the intervention, during the bed turning procedure, and 30 minutes after the bed turning procedure (Figure 1, T_0_-T_3_). Pain assessments will be performed using validated tools as recommended in ICU clinical practice guidelines [1]. For all patient participants, the CPOT will be used because it is one of the most valid behavioral scales for assessing pain in critically ill adults [42]. In addition to the CPOT, patient participants able to self-report will be asked to rate their pain intensity using the 0-10 Faces Pain Thermometer [43] and their pain distress on a 0-10 NRS [44,45].

### Data Analysis

#### Overview

A data bank will be created with the SPSS software (version 27.0; IBM Corp) [46], where the collected data on acceptability, feasibility, and preliminary efficacy will be entered. All the statistical analyses described below will be performed using SPSS.

#### Acceptability of the Intervention

The acceptability of the POMI will be determined using the TAP questionnaire. The frequencies, medians, and IQRs will be calculated for each item as well as for the total score, which will be calculated by taking the median, out of 4, of all items. The first 4 items (suitability, appropriateness, perceived effectiveness, and willingness to comply) will be scored in sequence (with 0 being the least favorable and 4 being the most favorable), whereas the last item (risks or side effects) will be scored in reverse (with 4 being the least favorable and 0 being the most favorable), as it is a negatively worded question. Any notes or comments added to the ratings will be compiled by category and presented descriptively to accompany the numerical ratings. A median above 2 out of 4 for the total score will be considered as an acceptable intervention, overall. An item median score above 2 out of 4 will be considered an acceptable attribute of the POMI. A median below 2 out of 4 will indicate the need to look more closely at the comments accompanying the ratings and modify the intervention to improve the acceptability of the POMI (eg, mode of delivery and dose). The acceptability of the POMI will be established via data triangulation from all study participants: patients, family members, and nursing staff [47].

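### The risks or side-effects item is worded with 4 as the worst score, but the rule that a median above 2 is acceptable is applied to it unchanged

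*Protocol article*

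**What the plan says.** The Outcomes section on acceptability describes a four-item TAP scale rated 0 to 4, on which higher means more acceptable. It then reports that "1 item has been added to the questionnaire to determine the risks of side effects of the POMI".

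The Data Analysis section, under Acceptability of the Intervention, sets the scoring and the decision rules:

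- The first four items "will be scored in sequence (with 0 being the least favorable and 4 being the most favorable").
- The risks or side-effects item is to be scored in reverse, "with 4 being the least favorable and 0 being the most favorable", on the ground that the question is negatively worded.
- The summary across items is "the total score, which will be calculated by taking the median, out of 4, of all items".
- The item rule is "An item median score above 2 out of 4 will be considered an acceptable attribute of the POMI".
- The overall rule is "A median above 2 out of 4 for the total score will be considered as an acceptable intervention, overall".
- In the other direction, "A median below 2 out of 4 will indicate the need to look more closely at the comments accompanying the ratings and modify the intervention".

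No sentence exempts the fifth item from these rules, and none says that its values are transformed before they are applied.

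**The concern.** The thresholds make sense only if a higher score is better on every item to which they apply. As worded, the fifth item runs the other way. A group reporting no side effects would then fall on the modify side, and a group reporting the maximum would be classed as finding the attribute acceptable. The same values would also enter the total with the wrong sign.

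Acceptability is a primary objective, and the Preliminary Efficacy section recommends a full-scale trial only if the intervention is found acceptable and feasible. The fifth item is the only one on the questionnaire that asks about harm. Two analysts who read the scoring sentence differently could report opposite verdicts on it from the same data.

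**Working it through.** There is no figure of the plan's own to reproduce. The check applies the written rules to the scores as worded, and again after recoding the fifth item.

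**Inputs (all from Data Analysis, Acceptability of the Intervention).** Items 1 to 4 are scored 0 to 4 with 4 best. Item 5, r, is scored 0 to 4 with 4 worst. The rule is: median above 2 acceptable, below 2 modify, exactly 2 given no verdict. The total is the median of the five items.

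**Step 1: the item verdict.** Recoding replaces r by 4 − r. Since median(4 − r) = 4 − median(r), an item median m becomes 4 − m.

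| Median of item 5 as worded | Rule as written | After recoding (4 − m) |
|---|---|---|
| 0 (most favorable) | modify | 4, acceptable |
| 1 | modify | 3, acceptable |
| 2 | neither | 2, neither |
| 3 | acceptable | 1, modify |
| 4 (least favorable) | acceptable | 0, modify |

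The verdict reverses at every value except 2. This also covers half-point medians, because m > 2 is the same condition as 4 − m < 2.

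**Step 2: the total for one respondent.** The median of five scores exceeds 2 exactly when at least three of them do. Let k be the number of items 1 to 4 scored 3 or 4.

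- k = 3 or 4: the total is above 2 whatever item 5 is. Patterns: (4 × 2³ × 3 + 2⁴) × 5 = (96 + 16) × 5 = 560. None change.
- k = 0 or 1: the total cannot exceed 2. Patterns: (3⁴ + 4 × 2 × 3³) × 5 = (81 + 216) × 5 = 1,485. None change.
- k = 2: item 5 decides. There are 6 choices of the two high items, 2² = 4 ways to score them and 3² = 9 ways to score the other two: 6 × 4 × 9 = 216 combinations, or 216 × 5 = 1,080 patterns. The verdict as worded needs r = 3 or 4; the recoded verdict needs r = 0 or 1. They disagree at four of the five values of r: 216 × 4 = 864.

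Check: 560 + 1,485 + 1,080 = 3,125 = 5⁵. The changed share is 864/3,125 = 27.6%. Of these, 216 × 2 = 432 are acceptable only as worded and 432 only after recoding. A full enumeration agrees. If a move between exactly 2 and below 2 is also counted as a change, it gives 1,344 of 3,125 (43%).

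**Step 3: examples.**

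- Items 3, 3, 2, 2: with r = 4 the total is 3 as worded and 2 recoded; with r = 0 it is 2 as worded and 3 recoded.
- Items 3, 3, 1, 1 with r = 4: 3 (acceptable) as worded, 1 (modify) recoded.
- Items 4, 4, 4, 4: the total is 4 either way.

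**The case against.** The strongest reply is that the authors did specify a recode. Reverse scoring a negatively worded item normally means turning it to match the others, and the stated reason, that the question is negatively worded, makes sense only if alignment was the aim. On that reading the parenthesis describes the raw answers. This may well be what was intended, so a reader who infers that the plan definitely leaves the item unrecoded, or that high risk will be declared acceptable, goes further than the text allows. What remains is that the parenthesis parallels the one for items 1 to 4, which plainly describes the scores used. After a true reversal 4 would be the most favorable score, and the text says the least.

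Three other strong inferences also fail:

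- **That a no-risk result automatically changes the intervention.** A median below 2 first sends the team to the comments accompanying the ratings, which would probably expose the misdirection.
- **That this item drives the recommendation for a full-scale trial.** The overall rule rests on the total, and a median of five resists one discordant item. Where respondents largely agree on the other four items, nothing changes.
- **That there is a 28% chance of a wrong conclusion.** The 864 patterns are weighted equally and describe single respondents, whereas the plan judges medians across respondents.

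Item frequencies and interquartile ranges are also to be reported, so the error could be seen and undone from the data. Triangulation across patients, families and nursing staff helps less, because nothing indicates that the item is scored differently for any of them.

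**Conclusion.** The scoring sentence for the risks or side-effects item conflicts with the decision rule that follows it. Read literally, the item-level verdict on risk is inverted at every median except 2. The effect on the total is limited: its above-2 verdict changes only for a respondent with exactly two of items 1 to 4 above 2, which is 864 of 3,125 unweighted patterns.

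This rests on the parenthesis meaning the scores as analyzed, and on the median total in the Data Analysis section; the Outcomes section describes the TAP total as a mean. If a recode was intended, the fault is one of wording, but it still leaves the direction of the item to the analyst. Because acceptability is a primary objective and a condition for recommending the next trial, the direction should be settled before the data are analyzed.

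**What to change.** State that the risks or side-effects item is recoded as 4 minus the raw score, so that 4 is the most favorable value, before any item or total median is computed. Alternatively, leave the item out of the total and give it its own rule, with a raw median below 2 acceptable. Either way, correct the parenthesis so that it matches.

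The cost is one sentence in the plan and, for the recode, one line in SPSS. Collected responses stay usable and no new data are needed. Confirm that the item has not already been reversed at data entry, so that it is not reversed twice.

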#### Feasibility and Fidelity of Intervention

Descriptive statistics will be obtained to compute the frequencies for each of the intervention feasibility items. The POMI will be considered a feasible intervention if there are no issues in over 50% of the items for the assessment of the intervention feasibility (as listed above) for at least 80% of the patient participants in each group [48]. Regarding the fidelity of the intervention, descriptive data will be computed on the amount of time spent creating the music playlists (≤10 minutes), delivery of the overall POMI (use of headphones or pillow), as well as the amount of time the music will be listened to (once, for at least 20 minutes). The percentage of items completed on the fidelity checklist will also be computed in order to ensure that at least 80% of the intervention fidelity items will be delivered as planned, yet to allow for a certain amount of flexibility, if needed [48,49].

#### Feasibility of Research Methods

Descriptive statistics will be generated for each of the feasibility of research methods items. The screening and recruitment procedures will be described and include the number of patients screened, the proportion of eligible patients as well as the number of enrolled participants. If less than 50% of the potential patient participants are found to be eligible, considerations will be made to broaden the inclusion criteria in an eventual full-scale RCT [39]. Time to recruit will be considered adequate if 24 patient participants are enrolled within 6 months. All issues related to recruitment will be described and grouped into categories by the student researcher.

The retention rates will be calculated and expected to be above 80%. Reasons for participant withdrawal will be described, when known, and if retention rates are below 80%, strategies will be recommended to reduce attrition, based on the reasons for study withdrawal. If more than 10% of the participants (in each group) are found to have missing data, reasons for missing data will be described to inform how to reduce the amount of missing data in future research.

#### Preliminary Efficacy

Descriptive statistics will be computed for all outcomes (CPOT, pain intensity, and pain distress scores). The 95% CIs will be computed for each dependent variable at each time point.

Considering the small sample size for a pilot study, the potential efficacy of the POMI will be analyzed using nonparametric tests. For the dependent variables (CPOT, pain intensity, and pain distress scores), the Friedman test will be used to compare the scores at individual time points in each group separately. If the Friedman test is found to tend toward significant (*P*<.10), the Wilcoxon signed rank test will be used to compare 2 timepoints in pairs with a Bonferroni correction (.05 per number of tests) to locate the differences.

The preliminary efficacy findings will not be used to inform the decision to pursue a full-scale RCT. However, any tendency toward statistical significance (*P*<.10) or significant lower pain scores in the music period versus the control period will support that the intervention group might decrease pain over time, compared to the control group. A formal hypothesis of efficacy will need to be tested in a full-scale RCT, which will only be recommended if the POMI is deemed acceptable and feasible.

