Another limitation in previous RCTs analyzed in the systematic review relates to sample size [9]. In 4 RCTs, no sample size calculation was reported [14-17]. In 3 RCTs, the sample size was calculated based on outcomes other than pain [18-20]. In another 3 studies, the calculated sample size required was not attained for various feasibility issues attributed to “slow” or “difficult” recruitment (due to time limit, refusal rate due to randomization or family visits, and narrow inclusion criteria), or withdrawal of ICU adult patient participants who did not like the music chosen for them [21-23]. In 1 study, it was unclear whether the sample size represented the number of ICU adult patient participants or the number of observations [24]. Inadequate power may explain why 11 of the 18 RCTs found a significant pain reduction while 7 did not. Therefore, there is a need to evaluate the feasibility of research methods by conducting a pilot RCT prior to evaluating the efficacy of any new music intervention in the adult ICU.

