## Discussion

### Methodological Strengths

One strength of this study is the evaluation of the intervention acceptability from multiple sources: ICU patients, families, and nursing staff. This will allow us to gain access to the different perspectives of the various stakeholders and acquire a more comprehensive understanding of the overall acceptability of the intervention. The crossover design is another strength as it allows each patient participant to be their own control, thus reducing confounding factors that are usually present in between-subject designs [50,51]. Moreover, the crossover design will allow for patient participants able to self-report to share their preference between the POMI and the CTL because they will experience both interventions. Information about participant preference will add rich qualitative data beyond the quantitative comparison of preliminary efficacy [41,51]. The crossover design is relevant to use during procedures that are planned within a short period of time (eg, molar extractions at 2 different times) [50]. In addition to intervention comparisons and patient participant preferences, we will be able to determine the pain and distress differences individually (numerically) and compute the proportion of patient participants for whom the treatment was effective in reducing pain by more than 1 point on a 0-10 NRS, for example [51]. The crossover design will also enable us to describe whether any reduction in pain or distress was qualified as meaningful by the patient participant (for those able to self-report). These data could later contribute to the understanding of the minimally clinically significant difference in procedural pain in the adult ICU population [51]. Knowing that patient participants will receive both interventions as part of the crossover design may allow them to think more objectively about pain levels in each intervention period (thus minimizing the placebo effect) compared to if they participated in a parallel-group trial, in which the patient participants’ hope to receive the intervention may influence their pain rating [50]. Finally, blinding patient participants unable to self-report will reduce the risk of bias based on these participants’ expectations of music efficacy to reduce pain.

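### Confidence intervals are planned for pain scores at each time point, but none for the within-patient music-minus-control difference on which the efficacy conclusion rests

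*Protocol article*

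**What the plan says.** All statements are in the protocol article.

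- Intervals (Preliminary Efficacy, under Data Analysis): "The 95% CIs will be computed for each dependent variable at each time point". The article mentions no other confidence interval.
- Main test (same section): "the Friedman test will be used to compare the scores at individual time points in each group separately".
- Follow-up test, used if the Friedman P value is below .10: "the Wilcoxon signed rank test will be used to compare 2 timepoints in pairs with a Bonferroni correction".
- Conclusion (same section): a P value below .10, or "significant lower pain scores in the music period versus the control period will support that the intervention group might decrease pain over time".
- Use of the result (same section): "The preliminary efficacy findings will not be used to inform the decision to pursue a full-scale RCT".
- Discussion, Methodological Strengths: the crossover is justified because patients serve as their own controls, and "we will be able to determine the pain and distress differences individually (numerically"). A proportion of patients improving by more than 1 point is offered as an example. Neither is given an interval or an SD, and neither appears in the Data Analysis section.
- Discussion, Methodological Limitations: the Friedman and Wilcoxon tests are said to serve the evaluation of the time effect, by subgroup.

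**The concern.** Three parts of the analysis text point at different quantities. The intervals describe how high pain is at one time point in one period. The tests, as described, ask whether pain changes over time within a group. The conclusion concerns music against control. The quantity that matches both the conclusion and the reason for a crossover is the difference within each patient, and it has no planned estimate or interval.

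If the section is followed as written, a reader of the results gets score levels for each period and P values. The reader is not told how large the music-minus-control difference was or how precisely it was measured. In a small pilot that leaves the formal efficacy hypothesis to a later trial, the estimate with its interval is the more informative output.

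**Working it through.** **The plan's own figure.** The Sample Size section starts from 10 per group and allows about 15% attrition: 10 / 0.85 = 11.76, rounded up to 12. Two self-report strata of 12 give 24, which matches the Randomization section (2 strata × 3 blocks × 4). The figure reproduces. The article gives no SD, within-patient correlation or target effect, so precision is shown below in units of the single-period SD, with the correlation ρ as an assumption.

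**Interval as planned (score level).**
Half-width = t(0.975, n−1) × SD / √n.
For n = 12: 2.201 / √12 = 0.635 SD. ρ does not enter.

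**Interval for the paired difference.**
SD of the difference = SD × √(2(1−ρ)), taking equal SD in both periods.
Half-width = t(0.975, n−1) × SD × √(2(1−ρ)) / √n.
For n = 12:
- ρ = 0.3: 0.635 × √1.4 = 0.75 SD
- ρ = 0.5: 0.635 × √1.0 = 0.64 SD
- ρ = 0.7: 0.635 × √0.6 = 0.49 SD

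**Other sample sizes.**

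| n | Score level | Paired, ρ = 0.3 | ρ = 0.5 | ρ = 0.7 |
|---|---|---|---|---|
| 10 (a stratum after the expected attrition) | 0.72 | 0.85 | 0.72 | 0.55 |
| 12 (a full stratum) | 0.64 | 0.75 | 0.64 | 0.49 |
| 24 (CPOT, all patients) | 0.42 | 0.50 | 0.42 | 0.33 |

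**What can be recovered from the planned output.** Without ρ, a reader could combine the music and control intervals only as if the two periods were independent. At n = 12 that gives 0.635 × √2 = 0.90 SD. This overstates the paired half-width by a factor 1/√(1−ρ): 1.20, 1.41 or 1.83 at ρ = 0.3, 0.5 or 0.7. The score-level interval is not simply too wide, since at ρ = 0.3 it is narrower than the paired one. It is an interval for a different quantity.

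**Allowing for period.** Average the mean music-minus-control difference of sequence 1 and that of sequence 2. With 6 patients per sequence the standard error is (SD of the difference / 2) × √(1/6 + 1/6) = SD of the difference / √12, as before, but on 10 degrees of freedom. The half-widths become 0.76, 0.64 and 0.50 SD, so the allowance costs almost nothing.

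**The case against.** The strongest reply has four parts.

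*Per-time-point intervals are legitimate description, and a condensed article need not list every output.* Both are true, and the sentence on intervals is not an error in itself. But the article does fix the interval target, the tests and the conclusion, and the first two do not match the third. That mismatch is in the text.

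*The signed rank test might be meant to pair a music time point with the corresponding control time point.* The wording does not exclude this. Even so, it would give a P value, with no estimate or interval.

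*Efficacy is secondary and kept out of the decision on a full-scale trial.* This stands, and it limits the weight of the point. The section still draws an efficacy conclusion, so that conclusion should rest on the matching quantity.

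*The pilot has no duty to size the next trial.* This also stands. A reader might infer that the next trial is left without a usable variance. The documents do not support that. No section gives the pilot this purpose. The follow-on design mentioned in Methodological Limitations is a parallel-group study, which needs the single-period SD that the planned descriptives can supply. The individual differences foreseen in the Discussion would also yield a paired SD, which matters only if the next trial is another crossover.

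A reader might also suppose that efficacy will be judged by whether the music and control intervals overlap. The plan states no such rule, so the power of such a rule is not a measure of what is lost here.

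**Conclusion.** The point holds as a mismatch between planned output and intended conclusion. The article plans no estimate or 95% CI for the within-patient music-minus-control difference, and the individual differences in the Discussion are not connected to the analysis section.

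At n = 12 the planned interval has half-width 0.635 SD at any correlation and so says nothing about the precision of the paired contrast, which would run from 0.75 to 0.49 SD for ρ from 0.3 to 0.7. These figures assume equal SDs in the two periods, complete pairs and t-based intervals for a mean. The correlations are assumptions, because the article gives none. The gap affects what is learned about preliminary efficacy. It does not touch the acceptability or feasibility objectives, and the data collected are sufficient to close it.

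**What to change.** In the Preliminary Efficacy section:

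1. Keep the per-time-point scores and their intervals, labelled as description.
2. Add the within-patient music-minus-control difference at T1, T2 and T3, with its 95% CI, as a Hodges-Lehmann estimate (in keeping with the nonparametric plan) or a mean difference.
3. Report the SD of these differences beside it.
4. Give CPOT per self-report stratum and overall, since all patients have it. Give pain intensity and pain distress for the patients able to self-report.
5. Preferably allow for period by averaging over the two sequences, and take the SD within sequence so that a period effect does not inflate it.
6. State that this contrast is the basis for the statement on the music versus the control period, and that it is the analysis of the individual differences mentioned under Methodological Strengths.

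The cost is one or two sentences and a few lines of code. No further data, visits or patients are needed. If a separate analysis plan already contains this contrast, a pointer to it is enough.

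### The named efficacy tests assess change over time, but the plan will draw a music-versus-control conclusion that no stated test or interval delivers

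*Protocol article*

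**What the plan says.** All references are to the Protocol article.

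- **Measurements** (Outcomes, Preliminary Efficacy of POMI on Acute Pain): "Pain will be assessed at 4 different timepoints for each intervention period". These are T0 before the intervention, T1 just after it, T2 during bed turning and T3 half an hour after turning.
- **Tests** (Data Analysis, Preliminary Efficacy): "the Friedman test will be used to compare the scores at individual time points in each group separately". A Friedman P value below .10 opens a second step, made of paired Wilcoxon signed rank tests between time points, each judged at .05 divided by the number of tests (Bonferroni).
- **Intervals** (same section): "The 95% CIs will be computed for each dependent variable at each time point".
- **Conclusion to be drawn** (same section): a tendency at P<.10, or else "significant lower pain scores in the music period versus the control period will support that the intervention group might decrease pain over time", relative to control.
- **Reason for the design** (Methodological Strengths): "The crossover design is another strength as it allows each patient participant to be their own control". This section also plans to look at each patient's differences numerically and, as an example, at the proportion whose pain falls by more than 1 point on a 0-10 scale.
- **Purpose of the tests** (Methodological Limitations and Mitigation Strategies): the Friedman and Wilcoxon tests are there to evaluate the time effect in each subgroup. Here the Wilcoxon test is called rank sum, not signed rank.

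**The concern.** The tests and the conclusion answer different questions. A Friedman test over T0 to T3 asks whether pain changes between time points. The conclusion concerns whether pain is lower with music than without it in the same patients. A crossover is chosen so that this second question can be answered by pairing each patient's two periods, and none of the named procedures uses that pairing.

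The sequence of measurements makes the gap matter. T2 falls during a procedure expected to hurt, so pain can vary over T0 to T3 in both conditions whether or not music works. A significant time effect in the music period could then be read as evidence for music. What is at stake is the secondary objective. The pilot might report P values that do not bear on it, and omit the paired estimate and its spread, which would be the most useful efficacy output for planning a larger trial.

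**Working it through.** **1. The plan's own figure.** The Sample Size section starts from 10 per group with about 15% attrition: 10 / (1 − 0.15) = 11.76, rounded up to 12 per group and 24 patients in all. This reproduces. No effect size or power for efficacy is stated, so the check below concerns what the tests respond to.

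**2. What each stated analysis compares.**

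| Stated analysis | What it compares | Tests or estimates music minus control within patient? |
|---|---|---|
| Friedman, by group | T0, T1, T2, T3 | No |
| Signed rank follow-up | Two time points; 4 × 3 / 2 = 6 pairs, .05 / 6 = .0083 | No |
| 95% CI | One score at one time point | No |
| Individual differences and responder proportion | A patient's own scores | Descriptive only; no test or interval |

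The stated conclusion needs a yes in the last column, and no row supplies one.

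**3. What a time-effect test responds to.** A simulation illustrates this. Its inputs are assumed, because the document gives none of them:
- scores of 0-10 rounded to whole points, with baseline mean 3;
- between-patient SD 1.5, period-to-period SD 0.7 within a patient, residual SD 1.2;
- no period or carryover effect; any music effect lowers T1 and T2;
- 1,500 runs per scenario, so the simulation standard error is √(.05 × .95 / 1500) = 0.6 percentage points near 5% and √(.5 × .5 / 1500) = 1.3 points near 50%.

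The direct comparison is a signed rank test at .05 on each patient's difference (T1 − T0 under music) − (T1 − T0 under control). Results for 12 patients:

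| Scenario | Friedman P<.10, music | Friedman P<.10, control | Direct paired test P<.05 |
|---|---|---|---|
| No music effect, turning adds 0 | 10.7% | 9.7% | 5.3% |
| No music effect, turning adds 1 | 52.5% | 52.9% | 5.1% |
| No music effect, turning adds 2 | 97.9% | 97.7% | 5.7% |
| No music effect, pain drops 1.5 by T1 in both conditions, turning adds 0.5 | 92.1% | 94.5% | 5.3% |
| Music lowers pain by 2, turning adds 2 | 97.3% | 98.3% | 63.0% |

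The Friedman columns follow the time profile and are nearly the same for music and control in every row, including the row with a real benefit. The paired test stays near 5% without an effect and responds when there is one. For the 2-point effect it rejects in 50.5% of runs with 10 patients and 92.0% with 24.

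**4. The follow-up step.** In the fourth scenario, a significant T1-versus-T0 drop at .0083 appears in the music period in 23.0% of runs and in the control period in 24.9%, although music does nothing. A within-condition drop therefore cannot be attributed to music without the paired contrast.

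**The case against.** **Efficacy is secondary and hedged.** Preliminary Efficacy says these findings will not inform the decision on a full-scale trial and that a formal hypothesis must be tested there. This stands, and it limits the severity.

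**The word *group* is ambiguous.** In Sample Size it appears to mean the able or unable to self-report stratum; at the end of Preliminary Efficacy it means intervention or control. If it means stratum, all eight scores per patient might enter one Friedman test, and some follow-up pairs would then compare music with control. The text does not say so, and the purpose given in the limitations section, the effect of time, speaks against it. The ambiguity is real, but it adds to the need for a correction.

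A reader might go further and infer that under this reading nothing could ever be significant. Eight scores give 8 × 7 / 2 = 28 pairs and .05 / 28 = .00179, while the smallest exact two-sided signed rank P with 10 patients is 2 / 2^10 = .00195. The document does not support that inference. The minimum is 2 / 2^11 = .00098 with 11 patients and 2 / 2^12 = .00049 with 12, the plan recruits 12 per group, and it never fixes 28 tests.

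**Rank sum could be a crossover test.** Applied to period differences between sequences, it would be the standard period-adjusted comparison. The limitations section ties it to the time effect instead and mentions no sequences. If that comparison was meant, it needs saying.

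**Within-patient differences are planned.** This is correct for description. It would be wrong to say that the plan ignores them; it attaches no estimate with interval and no test to them.

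**The follow-up step does respond to music.** With the 2-point effect above, the T1-versus-T0 drop is significant in 47.5% of music periods and 0.3% of control periods. That separation depends on pain not falling in the control period, which only a direct contrast can establish.

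**Period and sequence adjustment** may properly be left to an analysis plan, and sequences are balanced by blocks of 4 within stratum. Its absence from the article is no finding.

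**Conclusion.** The point holds at moderate severity. The article fixes both the tests and the conclusion, and the first do not deliver the second. This is a contradiction within the stated plan, not detail awaiting an analysis plan, and it needs no numerical assumption.

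The size of the possible misreading does depend on assumptions. For a trial of 12 with no music effect, the chance of a Friedman P<.10 in the music period ran from 11% to 98% as the assumed turning effect went from 0 to 2 points. Other SDs or profiles would give other figures.

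A reader might infer that the investigators will declare success when music is significant and control is not, and quote an error rate for that rule. The plan never states such a rule; its criterion is lower scores under music than under control, with no test attached. Nor do the documents support the view that the pilot as a whole is compromised: acceptability and feasibility are unaffected.

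**What to change.** 1. State that the efficacy contrast is the within-patient POMI-minus-CTL difference, for example at T1 and T2, and say which time point leads.
2. Report it as a Hodges-Lehmann estimate with 95% CI and a signed rank test, or the 2x2 period-adjusted equivalent, which compares period differences between the two sequences.
3. Use each period's T0 as baseline and fix in advance how. Under the assumed SDs, subtracting T0 gives a paired SD of √(4 × 1.2²) = 2.40, against √(2 × (0.7² + 1.2²)) = 1.96 for the plain T1 difference, so covariate adjustment may be preferable to subtraction.
4. Keep the Friedman test and its follow-up as a description of the time course, and attach the stated music-versus-control conclusion only to the contrast in item 1.
5. Replace *group* by condition, stratum or sequence wherever it occurs in the analysis sections.
6. Reconcile signed rank (Preliminary Efficacy) with rank sum (Methodological Limitations and Mitigation Strategies).

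No new data are needed, since T0 to T3 are collected in both periods. The cost is a dated amendment to the analysis, preferably before outcomes are examined by condition. The abstract reports 22 of the 24 patients recruited by July 5, 2022, so the date should be recorded openly.
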